## Abstract

**Introduction:**

Interscalene brachial plexus block (ISB) is the first-line analgesic technique for arthroscopic shoulder surgery, but it is associated with a > 90% incidence of ipsilateral hemidiaphragmatic paresis (HDP), which severely limits its application in patients with preexisting pulmonary dysfunction. All currently available modified nerve block techniques have failed to achieve a 0% incidence of HDP while maintaining satisfactory analgesic efficacy. Our preliminary study demonstrated that subparaneural injection of 2 mL 0.375% ropivacaine at the bifurcation of the brachial plexus upper trunk provided excellent postoperative analgesia with no observed cases of HDP.

**Methods and analysis:**

This is a prospective, single-center, randomized, non-inferiority trial conducted at Ningbo No.6 Hospital, China. A total of 100 patients undergoing elective arthroscopic shoulder surgery will be randomized in a 1:1 ratio to receive either 2 mL or 5 mL of 0.375% ropivacaine via ultrasound-guided subparaneural injection at the upper trunk bifurcation. The dual co-primary endpoints are the pre-rescue Numerical Rating Scale (NRS) pain score immediately after full consciousness in the post-anesthesia care unit (PACU) (non-inferiority margin = 1 point) and the incidence of ipsilateral HDP assessed before PACU discharge. Secondary outcomes include diaphragmatic function parameters, pulmonary function, perioperative analgesic consumption, recovery indicators, and adverse events. All statistical analyses will be performed according to the pre-specified statistical analysis plan, with the intention-to-treat population as the primary analysis set.

**Clinical trial registration:**

http://www.chictr.org.cn, ChiCTR2500114139.

## Introduction

Shoulder pain is one of the most prevalent musculoskeletal disorders worldwide, affecting 7 to 34% of adults at any given time, with higher morbidity in women, elderly individuals, and manual workers (1, 2). In China, the annual prevalence of shoulder pain reaches 30 to 35% in the general adult population, and exceeds 50% in high-risk occupational groups, resulting in substantial productivity loss and medical resource consumption globally (3–6). For patients with rotator cuff injury and subacromial impingement syndrome—the leading causes of chronic shoulder pain, accounting for 44 to 78% of musculoskeletal shoulder pain cases—arthroscopic rotator cuff repair and subacromial decompression have become the mainstream surgical treatments worldwide, with over 370,000 procedures performed annually in the United States alone (7–10).

Despite the minimally invasive nature of arthroscopic shoulder surgery, patients often experience moderate to severe pain within the first 48 h postoperatively, with pain intensity comparable to that of open surgery (11). Traditionally, this postoperative pain is managed with opioid analgesics, the required dosage of which is similar to that for gastrectomy or thoracotomy (12, 13). However, opioid-based analgesia is associated with a series of adverse events including nausea, vomiting, pruritus and constipation, and even multimodal analgesia regimens fail to reduce opioid consumption significantly in patients undergoing rotator cuff surgery, driving the development of opioid-sparing regional anesthesia techniques (14–16).

Interscalene brachial plexus block (ISB) is currently the first-line opioid-sparing analgesic regimen for shoulder surgery, as it significantly reduces postoperative pain scores, improves patient satisfaction, and shortens hospital stay (17). Nevertheless, ISB has a critical and potentially life-threatening limitation: it is associated with a more than 90% incidence of ipsilateral hemidiaphragmatic paresis (HDP). [18–20]HDP leads to a 27% reduction in forced vital capacity (FVC) and forced expiratory volume in 1 s (FEV1), which is intolerable for patients with preexisting pulmonary dysfunction, who may develop life-threatening hypoxemia and respiratory distress after HDP occurs (18, 19). Paradoxically, these high-risk patients are also not candidates for general anesthesia alone, as anesthetics, analgesics, and muscle relaxants can further impair their respiratory function and worsen clinical outcomes (20, 21).

To reduce the risk of HDP, various modified nerve block techniques have been explored, including low-volume ISB, costoclavicular block, combined axillary and suprascapular nerve block and anterior shoulder capsule block. However, even low-dose ISB still has an HDP incidence of over 20%, and costoclavicular block, initially reported to have zero HDP risk, has been verified to have an HDP rate ranging from 7.5 to 50% in subsequent studies including our team’s previous work (22–24). Other aforementioned modified techniques remain clinically controversial, with multiple studies reporting insufficient pain control for arthroscopic shoulder surgery and high rates of rescue analgesia (25, 26). Recently, Zhang et al. reported that subparaneural injection of 5 mL ropivacaine at the bifurcation of the brachial plexus upper trunk achieved non-inferior analgesia compared with ISB, while reducing the HDP incidence to 16.7% (27). While this finding is promising, the 16.7% HDP risk is still unacceptable for patients with severe pulmonary impairment, as even minimal risk of HDP can lead to catastrophic clinical outcomes, following the “all-or-none” principle of HDP prevention (21). The minimal effective volume of local anesthetic for this technique, which could eliminate HDP risk while maintaining satisfactory analgesia, remains undefined.

Our team conducted a preliminary study enrolling 11 patients undergoing elective arthroscopic shoulder surgery, and found that subparaneural injection of 2 mL 0.375% ropivacaine at the upper trunk bifurcation provided excellent postoperative analgesia, with no cases of HDP observed in this small cohort. Based on these promising preliminary findings, we designed this trial to assess whether 2 mL of 0.375% ropivacaine provides non-inferior analgesic efficacy compared with 5 mL, while significantly reducing the incidence of HDP. If confirmed, the results of this trial may help define a potential ‘zero-risk dose threshold’ for this technique, and could provide a safer analgesic option for patients undergoing shoulder surgery, especially those with compromised pulmonary function.

## Methods

### Ethics and dissemination

The research protocol, informed consent form and all study-related materials of this trial have been reviewed and approved by the Ethics Committee of Ningbo No.6 Hospital (Ethics Approval No.X2025-14(K)-1). This prospective, single-center, randomized, non-inferiority trial has been prospectively registered at the Chinese Clinical Trial Registry (http://www.chictr.org.cn), with the trial registration number ChiCTR[2500114139] and registration date [December 08, 2025]. This study is conducted in strict accordance with the ethical principles of the Declaration of Helsinki, and follows the Consolidated Standards of Reporting Trials (CONSORT) guidelines for randomized controlled non-inferiority trials.

All participants will provide written informed consent prior to any study-related procedures during the preoperative anesthesia visit. All subjects reserve the right to withdraw from the study at any time without any penalty or negative impact on their routine perioperative clinical care and treatment. The personal identifiable information of all participants will be strictly encrypted and kept confidential, with access limited only to authorized research team members. All original study data, including signed informed consent forms, case report forms, ultrasound measurement records, and electronic medical records, will be securely archived and retained for at least 5 years after the completion of the study, in compliance with Good Clinical Practice (GCP) regulations and the requirements of the institutional ethics committee.

This protocol is written and reported in full adherence to the Standard Protocol Items: Recommendations for Interventional Trials (SPIRIT) guidelines. The detailed schedule of participant enrollment, interventions, and outcome assessments is presented in Figure 1, and the flow chart of patient screening, eligibility assessment, randomization, and follow-up is illustrated in Figure 2.

**Figure 1 fig1:**
[figure not shown]
Schedule of enrolment, interventions, and assessments for the randomized controlled non-inferiority trial.

**Figure 2 fig2:**
[figure not shown]
Flow chart of patient screening, eligibility assessment, randomization, and follow-up.

### Status and timeline

*Participant recruitment*: Recruitment of eligible participants is scheduled to initiate on January 1, 2026, and is anticipated to be completed by December 31, 2026, at the Department of Anesthesiology, Ningbo No.6 Hospital.

*Data collection*: Perioperative baseline data, intervention-related data, and primary and secondary outcome data collection will be conducted concurrently with participant enrollment, and is expected to be fully completed by December 31, 2026. Data quality verification and cross-check will be performed synchronously during the collection period to ensure the integrity and accuracy of the dataset.

*Data management and statistical analysis*: Data cleaning, database locking, and final quality audit will be completed from January 2027 to February 2027. Formal statistical analysis for the primary non-inferiority test and secondary outcome analysis will be conducted from February 2027 to June 2027, in strict accordance with the predefined statistical analysis plan.

*Results availability*: Preliminary analysis results will be available by June 2027. The final study results are expected to be fully reported and submitted for academic publication by December 2027, with the development and promotion of the standardized operation procedure initiated thereafter.

### Subjects and setting

We plan to enroll 100 patients scheduled for elective arthroscopic shoulder surgery at the Department of Anesthesiology, Ningbo No.6 Hospital, Ningbo, Zhejiang, China. Eligible participants will be randomized in a 1:1 ratio to the 2 mL group or 5 mL group, receiving 2 mL or 5 mL of 0.375% ropivacaine via ultrasound-guided subparaneural injection at the bifurcation of the brachial plexus upper trunk, respectively.

Inclusion criteria:

Aged 18 to 75 yearsScheduled for elective arthroscopic shoulder surgery under general anesthesia combined with brachial plexus blockAmerican Society of Anesthesiologists (ASA) physical status I–IIIBody mass index (BMI) ranging from 18.5 to 30 kg/m^2^Fully understand the study protocol and voluntarily sign the written informed consent form before any study-related procedures

The exclusion criteria will be as follows:

Refusal to participate in the study or inability to provide informed consentKnown hypersensitivity to amide local anestheticsPreexisting nerve injury or sensory abnormality in the operative upper limbHistory of surgery in the ipsilateral shoulder or cervical regionSuspected infection at the puncture site of the ipsilateral shoulder or neckPreexisting pulmonary disease confirmed by preoperative pulmonary function test (defined as FEV1/FVC < 70%)Coagulopathy (international normalized ratio [INR] > 1.5 or platelet count < 80 × 10^9^/L)Chronic pain condition requiring regular opioid medication for more than 3 months preoperativelyConcomitant mental, speech, or hearing impairment that hinders the completion of pain score assessment, diaphragmatic function and pulmonary function tests.

### Participants’ consent

One day prior to the surgical procedure, investigators [name] will perform eligibility screening on patients slated for elective arthroscopic shoulder surgery the subsequent day. For those patients who satisfy all the inclusion criteria and none of the exclusion criteria, the investigators will disclose the study-related details to the patients and their family members or legally authorized representatives in an easy-to-understand manner, with sufficient time reserved for the patients to ask questions and confirm details.

The disclosed information encompasses the study’s primary and secondary objectives, detailed procedural steps (including preoperative baseline measurement of diaphragmatic function and pulmonary function, ultrasound-guided subparaneural brachial plexus block at the upper trunk bifurcation, standardized general anesthesia management, and postoperative outcome assessment in the post-anesthesia care unit [PACU]), potential therapeutic benefits (effective postoperative pain control with reduced risk of hemidiaphragmatic paresis and respiratory-related complications), possible adverse events (including local anesthetic allergy, nerve injury, local anesthetic toxicity, intraoperative hypotension, postoperative nausea and vomiting, and other anesthesia-related complications), and corresponding risk-mitigation strategies. The investigators will also explicitly inform the patients that the study is for scientific research purposes only, and their participation will not incur any additional medical expenses beyond routine clinical treatment.

In the event that patients express their willingness to partake in the study after fully understanding all the above information, either they or their legally authorized representatives are required to sign the written informed consent form in triplicate. One copy of the signed form will be provided to the participant or their legal representative, one will be filed in the participant’s electronic medical record, and the third will be securely archived by the research team in the study-specific locked filing cabinet, in compliance with the requirements of the institutional ethics committee.

All participants reserve the unconditional right to withdraw from the study at any time, for any reason, without any penalty, restriction, or negative impact on their routine perioperative clinical care and treatment. For participants who withdraw from the study, the research team will continue to provide standardized clinical treatment and care in accordance with clinical guidelines, and will not discriminate against or retaliate against the participant in any form. For participants who withdraw before the completion of all study assessments, the research team will not collect additional follow-up data without the participant’s explicit consent; de-identified data collected before withdrawal will be retained for statistical analysis only after obtaining ethical approval. No individual identifiable information of the participants will be used in any research report or academic publication.

### Randomization and blindness

#### Randomization procedure and allocation concealment

This study uses a blocked randomization design with a fixed block size of 4 to ensure a strict 1:1 allocation ratio throughout the entire recruitment process. This design guarantees that after every 4 subjects are enrolled, there will be exactly 2 subjects in each group, eliminating any risk of significant group imbalance even in the presence of dropouts. The randomization sequence was generated by [name] using R software (version 4.4.3) with a fixed random seed of 13,579 to guarantee full reproducibility of the allocation sequence. A total of 100 eligible patients will be randomly assigned to either the 2 mL 0.375% ropivacaine group or the 5 mL 0.375% ropivacaine group.

Allocation concealment was achieved using the sequentially numbered, opaque, sealed envelopes (SNOSE) method, which is the gold standard for allocation concealment in single-center clinical trials. Each random allocation result was recorded on a pre-printed card, which was then placed into an individual opaque, non-resealable envelope. The envelopes were numbered sequentially from 1 to 100 and sealed to prevent any prior tampering or detection of the allocation result.

[name], who generated the randomization sequence, has no involvement in patient recruitment, intervention implementation, outcome assessment, or data analysis. The sealed envelopes are stored in a locked filing cabinet with restricted access, and only [name], the dedicated anesthesiology nurse responsible for study drug preparation, has access to the envelopes. When a patient meets all inclusion criteria and provides written informed consent, [name] will open the next sequentially numbered envelope immediately before the nerve block procedure, prepare the study drug according to the allocation result, and record the envelope opening time and group assignment in a dedicated study log.

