##### Data management governance and role allocation

An independent data management team consisting of two trained research assistants and one designated data manager is established for this trial. All members of the data management team have no involvement in the implementation of the study intervention, perioperative anesthesia management, baseline or postoperative outcome assessments, and randomization sequence generation, and remain fully blinded to the subject’s group allocation throughout the study. The specific responsibilities are clearly divided as follows:

The designated data manager is responsible for the overall design of the eCRF in the ResMan system, database establishment, hierarchical access control setting, and supervision of the entire data management process;The two independent research assistants are responsible for independent dual data entry, cross-verification, and discrepancy resolution in the ResMan system, with no communication with the study intervention anesthesiologist, outcome assessor, or study drug administrator regarding any content related to group allocation;[name], the dedicated anesthesiology nurse responsible for randomization sequence management and study drug preparation, is the only personnel with access to the complete randomization allocation list, and is prohibited from participating in any data management, data entry, or statistical analysis procedures. The randomization allocation list is stored in a separate encrypted module in the ResMan system, which will not be accessed by any personnel until the database is formally locked.

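### The article publishes the seed, R version and fixed block size of a list already drawn, which weakens allocation concealment, and its two statements on who may access the list conflict

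*Protocol article*

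**What the plan says.** Under *Randomization procedure and allocation concealment*, the Protocol article states: "This study uses a blocked randomization design with a fixed block size of 4". The sequence has already been produced in R 4.4.3 "with a fixed random seed of 13,579 to guarantee full reproducibility of the allocation sequence". The list length follows from the same section: "A total of 100 eligible patients will be randomly assigned to either the 2 mL 0.375% ropivacaine group or the 5 mL 0.375% ropivacaine group". The allocations are already in numbered, sealed, opaque envelopes. Of the study staff, only "the dedicated anesthesiology nurse responsible for study drug preparation, has access to the envelopes", and the nurse opens the next one after eligibility and consent, immediately before the block. The person who generated the sequence has no part in recruitment, intervention, assessment or analysis.

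*Status and timeline* has recruitment starting on 1 January 2026 and says that it "is anticipated to be completed by December 31, 2026".

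*Blinding procedures* limits knowledge of allocation to two people, the nurse and the anesthesiologist who performs every block. It bans communication about allocation with blinded staff.

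*Data management governance and role allocation* says that the nurse "is the only personnel with access to the complete randomization allocation list". The next sentence places the list in an encrypted module "which will not be accessed by any personnel until the database is formally locked".

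**The concern.** Sealed envelopes protect a sequence only if it cannot be obtained another way. The seed exists so that the sequence can be reproduced, and here it is published with the software version, block size, ratio and list length while unopened envelopes are planned to be in use. Reproducibility needs the seed to be archived. It does not need it to be public before the last patient is randomised.

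The small fixed block adds a second leak that does not need the seed. The article presents exact balance after every four patients as an advantage, but that property also lets an observer of past allocations deduce the end of a block.

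With sound concealment, even an unblinded operator can say nothing certain about the next patient. If the next assignment can be deduced or looked up, one breach of the communication ban could reach those who screen and consent patients the day before surgery. Knowing the next assignment before enrolment is what permits selective enrolment.

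The access wording matters for the same reason. The nurse needs only the next envelope, and no task described before lock requires the whole list.

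**Working it through.** **List length.** The plan gives no figure for predictability, so the only figure to reproduce is the number of assignments. With 40 per group and 20% dropout, 40 / (1 − 0.20) = 50 per group, or 100 in total, as stated. With blocks of 4 this is 100 / 4 = 25 blocks.

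**Predictability from block size 4 alone.** Input: two of each arm per block, giving 4! / (2! × 2!) = 6 equally likely orders. Take an observer who knows the block size and all earlier allocations and always guesses the arm with more places left.

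| Position in block | Chance assignment is certain | Chance best guess is right |
|---|---|---|
| 1 | 0 | 1/2 |
| 2 | 0 | 2/3 |
| 3 | 1/3 (first two alike: 2 of 6 orders) | 1/3 × 1 + 2/3 × 1/2 = 2/3 |
| 4 | 1 | 1 |

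- Certain in advance: (0 + 0 + 1/3 + 1) / 4 = 1/3, or about 33 of 100 assignments.
- Best guess right: (1/2 + 2/3 + 2/3 + 1) / 4 = 0.708, or about 71 of 100, against 50 by chance.

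The same enumeration for other known fixed sizes:

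| Block size | Certain | Best guess right |
|---|---|---|
| 2 | 50% | 75% |
| 4 | 33.3% | 70.8% |
| 6 | 25.0% | 68.3% |
| 8 | 20.0% | 66.6% |

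**What the seed adds.** Without it there are 6^25, about 2.8 × 10^19, possible lists. With seed, version, block size, ratio and N fixed, what remains unknown is the R routine and the arm coding. Let M be the number of programs someone might plausibly write. M is not in the documents and is assumed here. Treating a wrong candidate as agreeing with an observed block with probability 1/6, the expected number of wrong candidates still matching after k complete blocks is M × 6^(−k).

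- M = 100, k = 4 (16 patients): 100 / 1,296 = 0.08.
- M = 1,000, k = 6 (24 patients): 1,000 / 46,656 = 0.02.

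If the true program is among the candidates, someone with that history could single it out within the first quarter of recruitment and read off the rest. No attempt was made to regenerate the trial's list. A run with the printed seed would prove nothing by itself, because any seed with 25 permuted blocks of 4 gives a balanced list of 100.

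**Access to the list.** One sentence gives the nurse sole access to the complete list. The next says no personnel will access it before lock. If the first describes working access, the second is false. If the second holds, the first gives the nurse a right that is never used before lock.

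**The case against.** A reader might infer that allocations are already known in advance. The documents do not support that. The routine, package and arm coding are not printed, and no candidate list has been or could be matched to the trial's list from the article.

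A reader might also infer that the screening investigators or the blinded assessor could work out the next assignment from the article. As documented they cannot confirm it. Testing a candidate, and both block-size figures, require past allocations. The blinding section restricts these to the nurse and the block operator and forbids passing them on.

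Those two, in turn, have no documented means of selecting patients. The envelope is opened after eligibility and consent, the operator receives the drug only after baseline measurements are complete, and neither is given a screening role. One of the unblinded people, whose name is removed, is expressly barred from recruitment.

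The nurse's access may be read as a permission rather than actual use, so it is not evidence that the list has been consulted. Publication during recruitment is inferred from the planned dates, since the article as shown gives no publication date.

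All of this stands and limits the point to a weakness in concealment. It does not remove the point. The safeguards restrict who talks to whom and do not address a published seed. The block-size leak and the conflicting access sentences are in the text whatever the routine was.

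**Conclusion.** The point holds as an avoidable weakness in concealment. It is not a finding that the sequence is known or has been misused. For anyone holding past allocations, one third of assignments are certain and 70.8% can be guessed correctly from the fixed block of 4. If the list were recovered with the help of the seed, all remaining assignments would be known. The first two figures are exact. The last depends on the true program being among those tried, and the number of plausible programs is an assumption.

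Selection bias would further require that someone with this knowledge passes it to those who enrol patients, contrary to the communication ban. The point should be acted on if envelopes remain unopened. The two sentences on list access conflict and must be reconciled in any case.

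**What to change.** If envelopes remain unopened:

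- From the next complete block boundary, replace them with a sequence drawn from a new, undisclosed seed and undisclosed, randomly varying block sizes, for example 4 and 6. Avoid blocks of 2: once recognised, they are more predictable than blocks of 4. Moving to a known fixed size of 6 would gain little (25.0% certain, 68.3% guessed), so non-disclosure and variation are what matter.
- Leave the complete list with the independent sequence generator alone. Limit the nurse to opening the next envelope, and rewrite *Data management governance and role allocation* so that its access statements agree.
- State that the seed and block sizes will be released after database lock.

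If recruitment is already complete, reconcile the access wording and report the disclosure and the fixed block size as a limitation. Comparing results before and after a redraw could show little with 100 patients and should not be relied on.

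The cost is a new set of envelopes, a short amendment, and a possible final imbalance of a few patients (a difference of at most 3 between arms if recruitment stops inside a block of 6).
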